### Sample size

The study follows an explorative approach and aims to include as many cases as possible in all five centres during the field phase. A sample size of 300 participants provides a power of over 95% with moderate effects of the education programme (standardised difference of paired means of 0.4) with an exploratory significance level of 0.05 (two-sided). Due to an expected drop-out of less than 15%, the aim is to recruit 350 children and 350 adolescents/young adults for the study. This lost-to-follow-up is considered realistic from previous paediatric research projects, because the subjects in the current study will have frequent consultations with the team of the department of endocrinology due to their diagnosis. Approximately 160 *newly* diagnosed cases are expected to occur in all centres together during the observation period based on previous year’s occurrence. Therefore, a participation of 100 families with newly diagnosed children in the study seems realistic. To ensure the participation of the families until the last follow-up, a strict reminder management is carried out and gift cards are awarded among all participants who have completed all questionnaires.

Regarding the qualitative evaluation, we plan to conduct approximately 50 semi-structured interviews with patients, parents, professionals, and peers taking part or working in the education programme. Based on the explorative assumptions of qualitative research, the number or content of the interviews can be adjusted until theoretical saturation is reached.

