### Evaluation

The education programme will be quantitatively and qualitatively evaluated by means of standardised questionnaires, interviews and participating observations. For the quantitative evaluation, patients and their relatives who participate in the education programme are requested to fulfil online questionnaires at four time points: at baseline before participation in the education programme (t0), immediately after participation in the education programme (t1), and at a follow-up 3 months (t2) and 6 months (t3) after participation. Table 3 shows the questionnaires used at the different time points in the evaluation.

**Table 3 Tab3:** Questionnaires of the quantitative evaluation of the study

Subgroup of sample	Time point	Standardised questionnaires	Self-constructed items
Parents of children under 6 years (includes parents of newly diagnosed children under 6 years)	T0, T2, T3	Cantril ladder, WHO-5	Sociodemographic data, diagnosis-specific items, social support, gender, maleness and femaleness, shame, self-esteem, disease burden and general coping, knowledge
Parents of children older than 6 years (includes parents of newly diagnosed children older than 6 years)	T0, T2, T3	Cantril ladder, KINDL-R parents, WHO-5	Sociodemographic data, diagnosis-specific items, social support, gender, maleness and femaleness, shame, self-esteem, disease burden and general coping, knowledge
Children 6–13 years	T0, T2, T3	Cantril ladder, KINDL-R (version 7–13 years), CODI (for children older than 7 years), BIS (for children older than 12 years)	Sociodemographic data, diagnosis-specific items, social support, gender, maleness and femaleness, shame, self-esteem, disease burden and general coping, knowledge
Adolescents 14–17 years	T0, T2, T3	Cantril ladder, KINDL-R (version 14–17 years), CODI, BIS	Sociodemographic data, diagnosis-specific items, social support, gender, maleness and femaleness, shame, self-esteem, disease burden and general coping, knowledge
Young adults 18–14 years	T0, T2, T3	Cantril ladder, WHO-5, BIS	Sociodemographic data, diagnosis-specific items, social support, gender, maleness and femaleness, shame, self-esteem, disease burden and general coping, knowledge
Children and adolescents 6–17 years	T1		satisfaction with programme, short version
Young adults 18–14 years	T1	Adapted ZUF-8	satisfaction with education
Parents of all children and adolescents	T1	Adapted ZUF-8	satisfaction with education

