### Statistical methods

Descriptive statistics will be presented for the subsamples children (6–13 years), adolescents (14–17 years), young adults (18–24 years), and parents separately. Categorical variables will be reported as absolute and relative frequencies (with 95% confidence interval), normal distributed metric variables as mean and standard deviation, and skewed variables as median with interquartile range.

Pre-post comparisons (before vs. after training) will be conducted with statistical tests for paired samples (single-factor ANOVA with repeated measures, one-sample t-test, McNemar test) separately for children, adolescents, young adults, and parents. All tests are two-sided with a significance level of 0.05. However, *p*-values are considered exploratory, without adjustment for multiple testing. Missing data will not be imputed. No interim analyses are planned. A statistical analysis plan will be prepared prior to data analysis.

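### The named repeated-measures ANOVA without imputation is a complete-case analysis; selective non-response would bias the estimated change, and a likelihood-based model avoids part of this at almost no cost

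*Protocol article*

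**What the plan says.** Under Statistical methods, the article plans "statistical tests for paired samples (single-factor ANOVA with repeated measures, one-sample t-test, McNemar test) separately for children, adolescents, young adults, and parents". It adds "All tests are two-sided with a significance level of 0.05", calls the p-values exploratory, and states "Missing data will not be imputed". An SAP is to follow before the analysis.

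Under Evaluation (Table 3), the outcome questionnaires are given at T0, T2 (3 months) and T3 (6 months); T1 carries only satisfaction items. Study design describes a non-controlled study.

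Under Sample size, the plan reads "A sample size of 300 participants provides a power of over 95% with moderate effects of the education programme", with a "standardised difference of paired means of 0.4) with an exploratory significance level of 0.05 (two-sided". On attrition it says "Due to an expected drop-out of less than 15" per cent, and it sets recruitment targets of 350 children and 350 adolescents/young adults. Reminders and gift cards are planned to keep families in follow-up.

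**The concern.** A classical single-factor repeated-measures ANOVA needs a value at every time point for each person. Without imputation, a person with T0 and T2 but no T3 contributes nothing. The estimated change then describes only those who answered every survey, and it is unbiased only if answering is unrelated to outcome.

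That condition is open to doubt here. Follow-up is by online questionnaire on a subject that the Background section links to shame and anxiety. The Discussion reports that many people with DSD feel no need for training in a hospital setting. If those who gain least are less likely to keep answering, the change is overstated. With no control group, nothing offsets this.

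The article says the funder's scheme integrates care models into routine care after positive evaluation, so the direction and size of the change matter even in an exploratory study.

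**Working it through.** **1. The plan's own figures.** Inputs from Sample size: n = 300, paired standardised difference d = 0.4, two-sided alpha 0.05, drop-out below 15%.
- Power = Φ(d√n − 1.96) = Φ(0.4 × 17.32 − 1.96) = Φ(4.97), above 99.99%. The stated power of over 95% is true; 84 pairs already give 95%.
- Recruitment: 300 / 0.85 = 353, against 350 stated; 350 × 0.85 = 297.5. The figures agree closely.

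**2. Who is lost to the ANOVA.** The article gives no rate by visit, so the rates here are assumptions applied to the target of 350. The share missing at least one follow-up is m2 + m3 − P(both).
- 15% at each visit, independently: 0.15 + 0.15 − 0.0225 = 27.75%. The ANOVA keeps 350 × 0.7225 ≈ 253. Each T0–T2 or T0–T3 pair has about 297. The people discarded despite one usable follow-up number 350 × (0.2775 − 0.0225) ≈ 89.
- 7.5% at T2, the same people among 15% at T3: the ANOVA keeps about 297 and discards 350 × 0.075 ≈ 26 people with a T2 value.
- The same 15% miss both visits: the ANOVA keeps about 297 and discards no follow-up data.

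In all three cases power for d = 0.4 stays above 99.9%.

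**3. Bias.** T0, T2 and T3 were simulated as trivariate normal with common correlation 0.5 or 0.7 and no true change. Everyone has T2, and 15% miss T3 by a logistic model in which the odds of non-response rise 2- to 4-fold per SD of poorer change. Rates, odds ratios and correlations are assumptions. Results are in SD of change.

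| Non-response at T3 depends on | Complete-case bias at T2 | Complete-case bias at T3 | Maximum-likelihood bias at T3 |
|---|---|---|---|
| observed T2 change (missing at random) | 0.10–0.17 | 0.05–0.09 | about 0 |
| unobserved T3 change (missing not at random) | 0.05–0.08 | 0.10–0.17 | 0.07–0.12 |

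- With purely random loss, complete-case bias is zero within simulation error.
- In both rows the T0–T2 pair, using everyone with T2, has bias of about zero. The bias at T2 therefore comes from the listwise deletion itself.
- With a true change of 0.40 and non-response depending on the observed T2 change, maximum likelihood returns 0.40–0.41 at T3; complete cases return 0.45–0.49.
- In the second row, 0.07/0.10 = 70% and 0.12/0.17 ≈ 71% of the bias remains after maximum likelihood.

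**4. What such a bias does to a test.** With no true change and n = 297, rejection is approximately Φ(b√297 − 1.96), where √297 = 17.23.
- b = 0.05: Φ(0.86 − 1.96) ≈ 14%.
- b = 0.09: Φ(1.55 − 1.96) ≈ 34%.

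The nominal rate is 5%.

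**The case against.** Several objections have force.

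- **Three tests are listed, not one.** The one-sample t-test and McNemar test need only the pair compared, and the article does not say which time points enter the ANOVA. A reader might infer that the whole plan drops everyone who misses T2 or T3. The text does not support that: full listwise deletion applies to the ANOVA, and its three time points are inferred from Table 3. The pairwise tests still use selected completers; in the simulation the T0–T3 pair carries the same bias as the complete cases.
- **Every missingness input is assumed.** The article gives no rate by visit, no mechanism and no correlations. It expects drop-out below 15%, so larger biases obtained by assuming, say, 30% loss at T3 go beyond its own expectation and are not relied on here.
- **Retention is managed.** Reminders, gift cards, frequent clinic contact and completeness checks should reduce non-response. They do not make what remains random.
- **The p-values are exploratory and unadjusted.** No confirmatory 5% error rate is claimed, so the rejection rates only illustrate scale. The label does not remove bias from the estimate.
- **An SAP is announced.** Covariance structure and sensitivity analyses can properly wait for it. But the ANOVA and the no-imputation rule are already fixed in the article, and the point concerns those two choices.

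Two further readings should be resisted. One is that the lost records threaten power; with 84 pairs sufficient for 95% at d = 0.4, they do not at the planned size. The other is that a mixed model cures the problem; it does so only if non-response depends on observed data.

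**Conclusion.** The point holds in a conditional form. If T0, T2 and T3 enter the named ANOVA, the two stated choices together make it a complete-case analysis. Whether this biases the result, and by how much, depends on a non-response mechanism that the article does not describe. For 15% loss at T3 driven by the observed T2 change, the overstatement at T3 is about 0.05 to 0.09 SD of change, up to roughly a fifth of the planned effect (0.09/0.4 = 23%). A likelihood-based analysis of the same data removes it. If loss is driven by the unobserved T3 change, the complete-case bias is about 0.10 to 0.17 and a likelihood-based model removes only about 30% of it.

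The harm is bias, not loss of power. Declining to impute is not itself the fault; the fault lies in pairing that rule with a method that needs complete records. The change should be made, because a better method uses data already being collected.

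**What to change.** In the SAP, before analysis:

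1. Make the main analysis of continuous outcomes a likelihood-based mixed model for repeated measures, with categorical time and unstructured covariance, using all available T0, T2 and T3 data. Fit it separately for the groups already planned. Report the T0–T2 and T0–T3 contrasts with 95% confidence intervals. No imputation is needed.
2. Keep the complete-case ANOVA as a sensitivity analysis.
3. Compare completers with non-completers on T0 values and T1 satisfaction, and report missingness by visit.
4. Add a sensitivity analysis for data missing not at random, for example a delta adjustment over a stated range, showing how much worse non-responders would have to do before the conclusion changes.

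The cost is SAP wording and slightly more analysis work. No new data, visits or participants are needed.

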### Qualitative evaluation

For the qualitative evaluation, two experienced researchers will perform semi-structured interviews and participatory observation. Preferably, interviews are conducted in a face-to-face situation, but can also be carried out as a telephone or video interview if required. All interviews will be recorded digitally, pseudonymised, and transcribed verbatim. Further data material contains the written memos and logbooks of the research process, interview protocols and observational protocols. These can add further information on the setting or nonverbal expressions of the interviewed or observed subjects. For the analysis, the transcripts are imported into the computer programme MAXQDA®. Data analysis is carried out by developing categories inductively from the material and deductively from the key themes of the interview guide. The analytic process will be circular, meaning that new insights from the interviews and initial data analysis will be included into possible revision of the interview guide and subsequent data interpretation. The analysis will be discussed in regular interdisciplinary team meetings to enhance intersubjectivity and multiperspectivity.

### Triangulation

In a further analysis step, the quantitative and qualitative study results will be triangulated, i.e., related to each other. This will allow to supplement, extend, and deepen the findings of the study, and will generate further hypotheses about the possible effects and experiences. The mixed-methods approach of this study follows a parallel design (quantitative and qualitative data are collected in parallel). The integration of quantitative and qualitative data is data- and outcome-based [50].

### Ethics

The study design follows the principles of the Declaration of Helsinki. The local ethics committee at the leading study centre Charité—Universitätsmedizin Berlin approved the study protocol, procedures, and consent forms (EA2/238/19). All participating study centres obtained ethical approval by their institutions.

## Discussion

Empower-DSD is a multicentre study to develop and evaluate an education programme for children, adolescents and young adults with DSD and their parents. This comprehensive education programme based on the ModuS concept [27] contains medical information as well as psychological issues arising from the diagnosis and is taught in an age-appropriate manner. From May 2020 to August 2022, the age- and diagnosis-specific education programme for CAH, Turner syndrome, Klinefelter syndrome and XX- or XY-DSD are provided at five study centres in Germany and will be evaluated quantitatively and qualitatively. This paper reports on the curriculum development process, the study design, and the evaluation concept.

As a first result of the Empower-DSD study, a specific DSD patient education programme is developed. For each diagnosis and for each age group (children, adolescents and young adults, parents/carers), a separate curriculum specifies learning objectives, content, and learning methods. Each manual includes an exemplary schedule for the implementation of the education programme. According to the manuals, the advanced DSD training academy was established and a total of 56 professionals, e.g., medical doctors, psychologists, social workers or medical assistants, were qualified to conduct the educational programme in the different study centres. The education programme is offered in groups separated by age and diagnosis. Usually, an education course takes two days with a total of 12–14 lessons of 45 min each. The courses of the children/adolescents take place simultaneously with the training of parents/carers. The groups are limited to 4–8 families. Furthermore, peer counsellors are an integral part of the educational programme. At each date, a peer from the cooperating patient support group is available to talk about the peer’s own experience in daily life with the diagnosis and to answer questions. Up to this day, a total of 336 subjects have been enrolled in the study and took part in the educational programme. Meanwhile, there have already been educational events provided for each diagnosis at least once. After each event, a feedback discussion takes place and the trainers of a centre fulfil a structured feedback form including information on organisation, methods, positive and negative training experiences to improve the quality of the educational programme. In order to benefit from the experiences of the other study centres, regular online meetings are held between the trainers.

The modular patient education approach (ModuS) was developed for rare chronic diseases in childhood. It was shown that this programme has positive effects on quality of life, knowledge and disease burden [19, 27]. For that reason, this ModuS concept served as a base for the curriculum of the DSD education programme. The modular structure allowed an adaptation to the needs of the different diagnoses CAH, Turner syndrome, Klinefelter syndrome, and XX- or XY-DSD including MRKH. Although there is a manual for every diagnosis, there are different themes which were developed once and could be used across all diagnoses, e.g., the explanations of chromosomes, hormones, pubertal development and others. On the other hand there are specific themes which are important for only one diagnose, e.g., the whole module 4 including competencies for the prevention and management of acute crises which was only included in the CAH programme. Next to the medical information, the psychosocial aspects are a main part of the programme under the assumption that psychosocial issues are at least equally as important as medical issues [19]. In the care of people with DSD, psychosocial care is obviously needed and should be an integral part of management [51, 52]. The psychological learning objectives were developed across all diagnoses, but have to be modulated to special needs for every single diagnosis.

All modules have been adapted for the inclusive language and for special issues comprising the DSD diagnoses. Finding a common language was a major challenge. Thus, modifications had to be made in terms of the inclusive language used, e.g., the word “diagnosis” is used instead of “disease” or the word “difference” instead of “disorder”. Here, the involvement of the patient support groups in the development of the trainings was a very valuable process [53, 54]. Some of the patient support groups had difficulties with embedding the education programme in a medical system, while others did not. The pathologising of their difference of sexual development as a “disease” was seen critically by many people with DSD. Since they do not consider themselves as being ill, they feel that they have no need for training in a hospital setting. Due to the rarity of the diagnoses, this is also a challenge in terms of recruitment. In a constructive and discursive process with the patient support groups, an attempt was to integrate all these perspectives in order to develop the best possible programme for the participants. These discussions can also be found in creating the evaluation contents. The development of the interview guides for the qualitative study part were circulated in the whole study team including the support groups and discussed intensively. The same process took place in the development of quantitative questions, e.g., about diagnosis-specific knowledge. This approach was intended to ensure an education programme with comprehensive, age-appropriate information and also information relevant for everyday life for the participants. The training of children, young people and parents in different groups addresses the different needs in knowledge transfer. Particularly for adolescents and young adults, special emphasis was placed on the examinations that will also be necessary later in life in order to improve the transition to adult medicine. In case of a necessary hormone replacement therapy, adherence can be improved by providing good and comprehensive information on the effects and side-effects of medical treatments [55].

In addition, in terms of learning methods, the needs of the different age groups had to be considered. Children and juveniles need a more playful approach to the content, while parents benefit from informative presentations and the group discussions with other families and experts [27]. For youth, learning objectives related to transition are an important element in increasing transition skills, self-efficacy, and satisfaction with school [56]. In general, the social contact and informal exchange are at least as important as the lessons on medical and psychological topics. The educational programme offers a protected setting to address individual concerns with psychological experts and peers with the aim to reduce diagnosis-specific burden and to improve the HRQoL [19]. Empowerment and self-management as main objectives of the ModuS concept are also taken into account in the DSD curriculum [27]. Due to the Sars-CoV-2-pandemic, we had to continuously reflect on whether these educations are also possible as online events, because the restrictions did not allow educations to be held in person for several months. However, the strength of the education programme is the interactive and communicative approach, which allows the participants to share their very sensitive and personal issues, which is probably not possible in an online course. So, we are looking forward to conducting further trainings in presence at our five study centres. In addition to the scientific evaluation, there is continuous reflection on the trainings, and at the end of the study the results will be incorporated into the revision of the curriculum.

The present protocol describes the aims, study design and methods of a newly developed age-specific multidisciplinary DSD education programme to improve the diagnosis-specific knowledge, skills and empowerment of children, youth and young adults with DSD and their parents. Empower-DSD will reduce knowledge gaps regarding the feasibility, acceptance and effects of standardised patient education programmes and will help to develop better multidisciplinary and integrated treatment strategies of high quality for children and young adults with DSD and their families.

## Data Availability

The datasets generated and analysed during the current study are available from the corresponding author on reasonable request. A specific research objective must be presented by an exposé.

## Abbreviations

CAH: Congenital adrenal hyperplasia
CODI: Coping with a disease
DSD: Differences of sexual development
HBSC: Health Behaviour in School-aged Children study
HRQoL: Health-related quality of life
ModuS: Modulares Schulungsprogramm (Modular education program for chronic diseases in childhood)
MRKH: Mayer-Rokitansky-Küster-Hauser syndrome
QoL: Quality of life
RedCap: Research Electronic Data Capture
WHO: World Health Organisation
